#### Clinical endpoints

Since physical rehabilitation and recovery of functional resources after ICU hospitalization are associated with the preservation of muscle mass, the present project hypothesizes an impact of our passive training interventions on the clinical rehabilitation outcome. Therefore, the following endpoints will be recorded before and after the intervention period, by discharge from the ICU and hospital as well as during rehabilitation:*Hospitalization and mortality*: Length of ICU stay, length of mechanical ventilation, length of hospital stays, hospital readmission rate, hospital- and 28-day mortality.*Health-related quality of life and return to work*: WHODAS 2.0 on the day of discharge, 6 and 12 months after discharge, return to work rate, job level compared to previous status

#### Underlying mechanisms and physiological consequences by intensive care therapy and interventions

Given that the patient population included in this study can only be examined under certain conditions due to the state of sedation or mechanical ventilation, additional outcome parameters that can be collected independently of patient cooperation were selected. Furthermore, the selected endpoints make it possible to describe the internal load of the applied interventions, as well as to monitor the acute impact of the life-threatening disease and intensive therapy on changes in muscle metabolism and inflammation over the time of intervention:*Intramuscular measurements*: By implementing a microdialysis catheter (µDialysis, Stockholm, Sweden) into the *M. vastus lateralis*, which remains in the muscle for 8 days, it is possible to continuously measure metabolic impact (e.g., lactate, glucose, pyruvate) and inflammatory cytokines (e.g., IL-6, IL-8, IL-10, and TNF-α) of the ICU therapy and intervention on the muscle tissue. This minimally invasive technique enables the quantification of the acute influence of therapy on muscle tissue and to correlate it with changes in the other dimensions of the endpoints.*Systemic immune response*: For comparison between intramuscular immune responses to the disease, ICU therapy and the applied interventions, systemic immune response will be measured by analysis of inflammatory cytokines (TNFa, Interleukins) dependent on NFkB signaling [26] from the microdialysis samples and patient serum samples.

### Trial design {8}

This study is a prospective, randomized controlled trial within the clinical routine intensive care treatment of patients with a four parallel group study design (Fig. 1): (1) Sham-Control Group (Sham-BFR/IPC); (2) blood flow restriction/ischemic preconditioning (BFR/IPC) training; (3) electromyostimulation (EStim), and (4) BFR/IPC-Training + EStim.

**Fig. 1 Fig1:**
[figure not shown]
Trial design

It aims to investigate the feasibility, safety, and potential efficacy of passive physiotherapeutic interventions—blood flow restriction/ischemic preconditioning (BFR/IPC), electromyostimulation (EStim), and a combination of both—in patients with ICU-acquired weakness (ICUAW).

The primary hypothesis is:

Alternative hypothesis (H₁): Passive physiotherapeutic interventions (BFR/IPC, EStim, or both combined) are feasible and safe in ICU patients and lead to a measurable improvement in clinical and muscle-related outcomes compared to the sham control.

Null hypothesis (H₀): There is no difference in feasibility, safety, or clinical/muscle-related outcomes between passive physiotherapeutic interventions and the sham control.

The trial is not powered for definitive efficacy conclusions but will provide estimates and trends to inform future multicenter trials.

## Methods: participants, interventions, and outcomes

### Study setting {9}

The study protocol received approval from the local Ethics Committee of the University Hospital Bonn (Approval No.: 390/23) and is registered at the Clinical Trial Registry (DRKS00033592). The study will be performed at the intensive care unit (ICU) of the University Hospital Bonn (Bonn, Germany) as a cooperation between the Department of Anesthesia and Intensive Care and Department of Orthopedic and Trauma Surgery. All investigations and exercise sessions will be performed in the University Hospital Bonn.

### Eligibility criteria {10}

Patients will be recruited on the ICU of the University Hospital Bonn. The patient inclusion criteria are as follows: (1) The study includes all patients under intensive care monitoring and therapy with a length of stay > 48 h in the surgical intensive care units of the University Hospital Bonn. (2) All participating patients have signed the patient consent form for study participation as well as the privacy policy after comprehensive explanation, explanation and information or have been represented by the spouse as part of the spouse’s emergency representation after comprehensive explanation. (3) Patients aged > 18 years are included. Exclusion criteria for the study are: (1) acute or chronic infections of the extremities, (2) open wounds on the lower extremity, (3) Pregnancy and breastfeeding, (4) sickle cell anemia, and (5) former surgical interventions on the thigh vessels (e.g., stenting, bypassing).

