#### Practical problems and potential passive solutions

Current guidelines for intensive care therapy recommend early mobilization of patients to prevent ICUAW. In clinical practice, however, physiotherapy exercises for ICU patients are extremely complex, only manageable with a considerable number of staff, and can rarely be carried out to the full extent, especially in sedated and intubated patients. An increasing shortage of personnel resources reduces the possibility of daily physiotherapy services as well. However, meta-analyses show that even early mobilization, if feasible, is not associated with a lower ICUAW prevalence or shorter ICU length of stay [12, 13]. These results could be due to two different reasons: (1) the interventions carried out were not intensive enough to provide the necessary stimulus to counteract muscle atrophy or (2) physical therapy treatment is unsuitable in the critical illness phase, as this is perceived as additional stress for the body or muscle preservation is physiologically not possible in this phase.

Therefore, the primary objective of this study is to investigate the clinical feasibility and safety of exclusively passive physiotherapeutic interventions in critical illness. The applied interventions, which consist of purely metabolic (blood flow restriction/ischemic preconditioning, BFR/IPC training), mechanical (electromyostimulation, EStim), or combined metabolic/mechanical load (BFR/IPC + EStim), will additionally be examined for their effects on the course of intensive therapy, physical and mental health/compliance of patients, and clinical outcomes (e.g., length of intensive care stay, length of hospital stay, prevalence of ICUAW, rehabilitation). It is intended that the results of this study will serve as a basis for subsequent projects regarding muscle metabolism and exercise therapy in ICUAW in a multi-center approach.

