#### Discussion of evidence

ICUAW shows a prevalence around 48% (95% CI, 39%, 56%) and is associated with an average loss of muscle mass of around 2.1%/day (M. rectus femoris: 95% CI, − 3.17, − 1.02) (level of evidence, LoE [14]: 1 A, 3.251 patients; [15]). Among these, older patients with pre- or sarcopenic conditions are particularly vulnerable to ICUAW and show higher ICU mortality, which is related to substantial loss of muscle mass (LoE: 1 A, 3.249 patients; [16]). The diagnosis of ICUAW is determined by sonographic muscle measurement in 85% of the studies included in meta-analyses (LoE: 1 A; [17]). The development of ICUAW is associated with a prolonged duration of mechanical ventilation, longer ICU and hospital stays, and mortality (LoE: 1B, 415 patients; [18]) and has a negative impact on rehabilitation after hospital discharge. Meta-analyses report increasing healthcare-related costs, 1-year mortality, and when it comes to survival after the ICU period, reduced physical activity outcomes compared to control groups over several years after hospital discharge (LoE: 1 A, 1.755 patients; [19]). These data can also be confirmed by observations from our research group that showed significantly reduced health-related quality of life in all tested domains, including mobility, life activities, and self-care. This was examined, using the WHO Disability Assessment Scale 2.0, 1 year after ICU discharge in patients who survived a long-term ICU-stay (unpublished data, data available for reviewers upon reasonable request).

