Because of the reduced recovery of ICU survivors, the search for interventions to counteract the development of ICUAW and its associated complications is intensifying. The “early mobilization” (EM) recommended in the S3 guideline of the German Society for Anesthesiology and Intensive Care Medicine e.V. (DGAI) “Lagerungstherapie und Mobilisation von kritisch Erkrankten auf Intensivstationen” shows only inconclusive results in the meta-analyses (LoE 1 A, 1.304 patients; [12]) without showing a positive effect on the rehabilitation of patients after discharge from the ICU. There is evidence of short-term effects on physical-related outcomes (LoE: 1 A, 709 patients, [20]) if physiotherapeutic exercise is started within the first 48–72 h of intensive care (LoE: 1 A, 1.726 patients, [21]). The insufficient outcomes are mainly attributed to the heterogeneity of the patient population, their reduced trainability (no possibility of active participation), and the limited feasibility in the hospital, as physiotherapeutic exercise of intensive care patients is associated with high costs and personnel resources.

Therefore, new intervention methods are needed that can provide sufficient training against the development of ICUAW, which are safe for patients and require few costs and human resources. Within this regard, electrical muscle stimulation (EStim) appears to be a safe intervention strategy which can associated with EM have positive impact on extubation success in ICU patients (LoE: 1 A, 1.312 patients, [22]). However, the quality of evidence for EStim to reduce ICUAW and improve rehabilitation after ICU discharge is low, mainly due to bias of the RCT trials and the heterogeneity of the enrolled population (LoE: 1 A, 140 patients; [23]).

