### Objectives {7}

ICUAW is a prevalent and severe complication in ICU patients, leading to significant muscle loss, prolonged hospital stays, and increased mortality. Despite the recommendation for early mobilization, existing interventions often fail to prevent or mitigate ICUAW due to practical constraints and insufficient intensity. This feasibility study aims to explore passive physiotherapeutic interventions—blood flow restriction/ischemic preconditioning (BFR/IPC) training, and electromyostimulation (EStim)—as alternative approaches which can be applied to all ICU patients, including those who are sedated or intubated. These techniques could circumvent the challenges of active physiotherapy and address muscle atrophy without exacerbating the patient’s condition or requiring extensive resources. By evaluating the safety, practicality, and effectiveness of these methods, the study seeks to address critical gaps in current ICU rehabilitation practices, potentially improving patient outcomes and reducing healthcare costs.

The present project aims to investigate these two questions by examining the effect of a purely metabolic (blood flow restriction/ischemic preconditioning (BFR/IPC) training), mechanical (electromyostimulation, EStim) or combined metabolic/mechanical load (BFR/IPC + EStim) on the physiology of the critically ill patient and clinical outcome (e.g., ICU length of stay, duration of hospitalization, prevalence of ICUAW, rehabilitation).

For this project, endpoints were defined that primarily reflect the clinical feasibility and safety of the intervention methods and their combinability with the clinical objective of muscle maintenance during ICU therapy and hospitalization. The following domains of outcomes include the evaluation of the impact of the interventions on the clinical rehabilitation process and the description of the underlying mechanisms of possible positive or negative effects on skeletal muscle physiology using invasive diagnostic monitoring.

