## Statistical methods

### Statistical methods for primary and secondary outcomes {20a}

#### Data acquisition

All patients will undergo the standardized study protocol. Per each day, measurements will be repeated thrice per time point. The median of these technical replicates will be used as the repeated measurement value for said time point. For descriptive purposes values will be reported as median ± interquartile range or absolute number and percent, where appropriate.

Primary analysis method will be an ANCOVA with Dunnett’s test with the measurement after 7 days as outcome and adjusted for the baseline value. Additionally, mixed models will be fitted to assess the sensitivity of the results under consideration of all measurement points. Health-related quality of life will be analyzed using mixed models for repeated measurements. Again, joint models may be considered to take a considerable proportion of missing data into account. Time-to-event outcomes, such as length of ICU stay, length of hospital stay, and time to return to work, will be analyzed using Kaplan–Meier estimates and Cox regression models.

All primary, secondary, and other exploratory outcomes will also be reported descriptively. Patients who decide to drop out of the study prior to completion of the intervention will remain in the study analysis and their respective study cohort following an intention-to-treat analysis. Recruitment will commence until the overall number of 120.

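### Entry sets no limit on prior ICU time and no rule on existing ICUAW, the target population is described in conflicting ways, and start time is left out of the muscle analysis

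*Protocol article*

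**What the plan says.** **Who may enter.** Eligibility criteria {10} of the protocol article takes adults "with a length of stay > 48 h in the surgical intensive care units". It does not say whether the 48 h must have elapsed or is the expected stay. The exclusions begin "Exclusion criteria for the study are: (1) acute or chronic infections of the extremities, (2) open wounds on the lower extremity" and go on to pregnancy or breastfeeding, sickle cell anaemia and earlier surgery on the thigh vessels. None concerns ICUAW or time already spent in the ICU.

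**Who the trial is about.** Trial design {8} places the aim "in patients with ICU-acquired weakness (ICUAW". Objectives {7} presents the interventions "as alternative approaches which can be applied to all ICU patients, including those who are sedated or intubated". Discussion of evidence argues for new methods on the ground that the development of ICUAW must be countered.

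**Timing.** Discussion of evidence says that ICUAW "is associated with an average loss of muscle mass of around 2.1%/day", with a confidence interval of 1.02 to 3.17% for the rectus femoris. It also reports short-term effects "if physiotherapeutic exercise is started within the first 48–72 h of intensive care".

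**Analysis.** Statistical methods {20a} fixes an ANCOVA with Dunnett's test "with the measurement after 7 days as outcome and adjusted for the baseline value", with mixed models as a sensitivity analysis. Sequence generation {16a} mentions no stratification. The section on additional analyses {20b} plans no subgroup or further exploratory analysis. ICUAW prevalence is a secondary clinical outcome (Abstract; Objectives {7}).

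**The concern.** A patient in the first days of the ICU stay and one who has been there for weeks are both eligible, and both get the same 7-day course and day-7 measurement. By the protocol's own account muscle is being lost throughout, so the two start from different points on that course. Three things follow.

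- The population statements cannot all describe the patients enrolled. Eligibility neither requires nor excludes ICUAW.
- Start time adds variation to the day-7 muscle value. Baseline thickness accounts for part of it only, because a naturally thin muscle early in the stay and a thick muscle already wasted can measure the same.
- ICUAW prevalence after the intervention includes cases that no study session could have prevented. That blurs its reading as an effect on new weakness.

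The trial is meant to pick out a promising arm for a later study (Sample size {14}), so avoidable noise and an unclear population weaken what is carried forward.

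**Working it through.** **Step 1: reproduce the planned power.** Inputs from Sample size {14}: difference 2.8 − 2.1 = 0.7 mm, follow-up SD 2 mm, correlation 0.9, 30 per arm, three comparisons with control. The error rate is not stated; I assume 5%, two-sided, familywise.

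- Residual SD = 2 × √(1 − 0.9²) = 0.872 mm
- Standard error = 0.872 × √(2/30) = 0.225 mm
- 0.7 / 0.225 = 3.11, against a Dunnett critical value of 2.380 on 115 degrees of freedom
- Power = 76.6% (75.4% in a direct simulation of 10,000 trials)

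This agrees with the stated figure of at least 75%.

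**Step 2: loss before entry.** At 2.1% per day, taken as linear, the loss is 3 × 2.1 = 6.3% on ICU day 3, 7 × 2.1 = 14.7% on day 7 and 14 × 2.1 = 29.4% on day 14. The planned effect is 0.7 / 11.2 = 6.3% of baseline thickness. These two percentages should not be compared directly: loss before entry is already in the baseline value, for which the ANCOVA adjusts. Only what baseline leaves unexplained adds noise.

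**Step 3: the part that baseline leaves unexplained.** Let A be thickness at admission, D the ICU day at entry and r the daily loss as a fraction of A. Then baseline B = A(1 − rD), and the loss over the next 7 days is 7rA. I assume D uniform over 3 to 14, because the documents give no distribution: mean 8.5, variance (14 − 3)²/12 = 10.08. A is scaled so that B has the protocol's mean of 11.2 mm and SD of 2.7 mm.

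- q = 1 − 8.5r; w = 10.08r²; mean of A: m = 11.2/q
- Variance of A: v = (2.7² − w·m²)/(q² + w)
- Variance of A not explained by B: v − q²v²/2.7²
- Extra residual SD: e = 7r × √(that variance)
- Total residual SD: √(0.872² + e²)

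For r = 0.021: q = 0.8215, w = 0.00445, m = 13.63, v = 9.52, unexplained variance 1.134, e = 0.147 × 1.065 = 0.157 mm, total 0.886 mm.

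| Daily loss | e (mm) | Total SD (mm) | Power | Change (points) |
|---|---|---|---|---|
| 1.02% | 0.032 | 0.872 | 76.5% | −0.1 |
| 2.1% | 0.157 | 0.886 | 75.1% | −1.5 |
| 3.17% | 0.388 | 0.954 | 67.7% | −8.9 |

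A separate check at 3.17% gave 68.5%, a loss of about 8 points, so the top of the range is 8 or 9. With entry confined to days 3 to 7 the loss at 2.1% is below 0.2 points.

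**Step 4: with ICU day as a covariate.** Simulating the same model with D added beside B (114 degrees of freedom), e falls to 0.007, 0.037 and 0.091 mm. Power returns to 76.6%, 76.5% and 76.1%.

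**The case against.** The strongest reply is that broad entry is deliberate. The protocol says "the primary objective of this study is to investigate the clinical feasibility and safety of exclusively passive physiotherapeutic interventions in critical illness", declares that it is not powered for definitive efficacy conclusions, and wants methods that sedated and ventilated patients can receive. Randomisation against sham gives a fair comparison whatever the mix of start times. All of this stands.

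A reader might infer that the trial cannot answer its stated question about preventing ICUAW. The documents do not support that. Prevention is background rationale; the primary objective is feasibility and safety.

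A reader might also infer that loss before entry, at several times the planned effect, swamps the comparison. Steps 2 and 3 show that most of it is absorbed by baseline.

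Nor does the 48–72 h evidence define a response window here. It concerns physiotherapeutic exercise, not passive cuff occlusion or electrical stimulation. How far permitted entry overlaps it depends on whether the 48 h is elapsed or expected stay.

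Two possible remedies carry real drawbacks. An upper entry limit would narrow the eligible pool and is a clinical choice. Restricting the ICUAW endpoint to patients shown to be free of it at baseline could drop many sedated patients, whom the protocol particularly wants to reach and who can be examined only under certain conditions.

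What the reply leaves standing is the conflict in the population statements, the unadjusted start time and the mixing of existing with new ICUAW.

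**Conclusion.** The point holds in a limited form. The population is described inconsistently, entry leaves prior ICU time and ICUAW status open, and the planned adjustment omits start time. The feasibility and safety aim and the validity of the randomised comparison are not affected.

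The cost in precision is about 1.5 power points at the protocol's central rate, and between almost none and 8 or 9 points over its confidence interval. This rests on linear loss, uniform entry over days 3 to 14, and the planning SD and correlation. The linear rate is itself uncertain: it gives 21% by day 10, against the 17% in 10 days quoted in Background and rationale {6a}. Later and wider entry would cost more.

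These figures cover noise only. If late starters also responded less, the effect would be diluted. For example, with an assumed 20% of patients not responding, the difference becomes 0.7 × 0.8 = 0.56 mm and power about 54%. The documents give no such share, so I do not count it in the size of the point.

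**What to change.** 1. Add ICU day at randomisation, known for every patient, as a covariate beside the baseline value in the day-7 ANCOVA and in the mixed models.
2. Reconcile Trial design {8} with Objectives {7}, Discussion of evidence and Eligibility criteria {10}. As eligibility stands, the population is patients with more than 48 h in the ICU, with or without ICUAW. State whether the 48 h is elapsed or expected stay, and that conclusions concern a mix of early and late starters. Whether to set an entry window is for the investigators.
3. Classify ICUAW at baseline as present, absent or not assessable, using the strength tests already planned before the intervention (Outcomes {12}). Keep all randomised patients in the ICUAW comparison, and report new cases among those free of it at baseline as a supportive result.

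The cost is one degree of freedom, one baseline field and some rewording. Trial status is given as in preparation, so on the article's account the changes can precede enrolment. The supportive result will rest on a subset, because many sedated patients will be not assessable; that is why it should not replace the comparison in all randomised patients.
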